In the setting of acute angle-closure attacks, patients can be instructed to perform ocular massage as an initial intervention to transiently lower IOP before definitive medical or surgical treatment can be administered [7,8]. Despite these promising clinical applications, previous studies have limitations that hinder drawing definitive conclusions about the underlying mechanisms and the sustained effectiveness of ocular massage [6,7]. Although the prior studies demonstrated temporary reductions in IOP after digital ocular massage, they were limited by the wide variability in the pressure applied by clinicians or patients and in the duration and frequency of massage because even small variations in finger placement or pressure can result in unpredictable IOP responses. These findings collectively highlight the potential clinical applications of ocular massage in various ophthalmic contexts [9]. EyePeace (Eye Comfort Ltd) is a commercially available device for eyelid massage designed to enhance meibum expression for dry eye disease related to meibomian gland dysfunction [10,11]. This flexible, handheld silicone device is used in conjunction with warm compress therapy and applies controlled vertical pressure to the closed eyelids [10,11]. EyePeace addresses the key limitations of manual digital ocular massage by offering a standardized, safe, and reproducible alternative. Unlike digital ocular massage, which is limited by inconsistent finger pressure, variable technique, and anatomical inaccuracy, EyePeace delivers calibrated and uniform mechanical force to the eyelids, ensuring consistent application across users and sessions. Its ergonomic design promotes proper positioning and motion, improving the reliability of therapeutic outcomes. By operating within safe pressure thresholds, EyePeace minimizes the risk of ocular complications such as hypotony, optic nerve stress, or retinal damage that may result from manual overcompression. In addition, its ease of use facilitates home-based therapy, enhancing patient adherence and long-term management. Originally developed for meibomian gland dysfunction, the device may also support aqueous humor outflow through gentle scleral compression, suggesting potential utility in select glaucoma settings. Overall, EyePeace offers a more controlled and patient-friendly approach that overcomes the variability and safety concerns associated with digital ocular massage.

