### Sample Size

On the basis of the stated assumptions (a common SD of 1.9 and a maximum mean difference in IOP between groups of approximately 2 mmHg), a total of 36 participants (72 eyes [participants will contribute both eyes unless exclusion criteria apply]; 3 groups; 24 eyes per group) are required to achieve 90% power at α=.05 [1,5]. This corresponds to 3 groups of equal size in a randomized controlled trial. The calculations use a 1-way analysis of variance to test overall mean differences and consider a moderate to large effect size in IOP reduction. Allowing for a 10% dropout rate, the recruitment target is 40 participants (80 eyes). If further data refine the expected mean difference, the sample size will be adjusted accordingly (larger samples for smaller expected differences and vice versa).

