### Statistical Methods

Following the guidelines for statistical analysis plans in clinical trials [18,29], all statistical analyses will be conducted using SPSS software (version 25.0; IBM Corp). The significance level is set at 5% (2-tailed), with a 95% CI. The normality of data distribution will be assessed using the Shapiro-Wilk test. Data will be compared using 2-way repeated measures analysis of variance. If the hypothesis is unmet (*P*>.05), the Greenhouse-Geisser correction will be applied. Multiple comparisons will be made between groups at different time points using the Bonferroni-Holm correction. If the Shapiro-Wilk test indicates that the data are not normally distributed (*P*<.05), nonparametric tests will be used: paired comparisons will use the Wilcoxon signed-rank test, and between-group comparisons will use the Kruskal-Wallis H test. Statistical significance will be considered at *P*<.05 for 2-tailed tests unless otherwise specified. To ensure participant safety, the distribution of AEs will be described for both digital ocular massage and EyePeace ocular massage groups. The incidence rates of AEs were compared using the chi-square test or the Fisher exact test, as appropriate. An intention-to-treat analysis will be the primary analytic approach. All participants will be included in the analysis based on their original allocation, regardless of protocol adherence. For missing data, multiple imputation will be performed using the fully conditional specification method, assuming data are missing at random. A sensitivity analysis using a per-protocol approach will also be conducted to compare results. Given the short duration of this study, an interim analysis will not be performed.

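### The only inference fixed for adverse-event incidence is a chi-square or Fisher test, which at 12 participants per arm says little about moderate excess harm; intervals should carry the safety reporting

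*Protocol article*

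**What the plan says.** The Statistical Methods section of the protocol article deals with AEs in two sentences. The first is descriptive: "To ensure participant safety, the distribution of AEs will be described for both digital ocular massage and EyePeace ocular massage groups". The second is inferential: "The incidence rates of AEs were compared using the chi-square test or the Fisher exact test, as appropriate". Neither says whether the unit is the participant or the eye, or whether the test compares two arms or three. The descriptive sentence names only the two massage groups.

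The same section says of the analyses in general: "The significance level is set at 5% (2-tailed), with a 95% CI". That phrase is not attached to AE rates or to a difference in rates.

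The Sample Size section rests on IOP alone, assuming "a common SD of 1.9 and a maximum mean difference in IOP between groups of approximately 2 mmHg". For 90% power at the 5% level, it gives the requirement as "a total of 36 participants (72 eyes [participants will contribute both eyes unless exclusion criteria apply]; 3 groups; 24 eyes per group". No AE rate, margin or safety power appears anywhere. Data Collection and Management and Monitoring both describe AEs as improbable in this population.

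**The concern.** A significance test on rare binary events in very small arms tends to return P>.05 whether or not one method is moderately more harmful. If that P value is the only inferential statement about AE incidence, the report has nothing to show how large a difference the data leave open.

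The risk of misreading is greater here because the Background already presents the device as the safer option, saying that "EyePeace minimizes the risk of ocular complications such as hypotony, optic nerve stress, or retinal damage that may result from manual overcompression". A nonsignificant AE comparison beside that statement could be cited in its support while carrying little information. At 12 per arm, 4 participants with an AE under one method and none under the other would be reported as not significantly different.

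**Working it through.** **Inputs**
- Arm size: 36 participants and 72 eyes (Sample Size), allocated 1:1:1 (Study Design). 36/3 = 12 participants and 72/3 = 24 eyes per arm.
- Recruited: 50 (Results). 50/3 = 16.7, about 17 per arm. Equal split is an assumption.
- Alpha: .05, two-sided (Statistical Methods).
- AE rates: none in the document. Assumed 0% to 10% in the reference arm and 20% to 50% in the other.
- Unit and contrast: participants, two arms compared. Also an assumption, since neither is stated.

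**The plan's own figure.** For three equally spaced means 0, 1, 2, the SD of the means is √(2/3) = 0.816, so f = 0.816/1.9 = 0.43. One-way ANOVA power from the noncentral F at 24 per group is 90.2%, and 24 is the smallest size that reaches 90%. Dropout: 36/0.9 = 40. The figure reproduces, with eyes counted as independent units. It concerns IOP only.

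**Step 1: what Fisher needs to reach P<.05.** With a events in one arm of n and none in the other, two-sided P = 2·C(n,a)/C(2n,a).
- n=12, a=4: 2×495/10,626 = .093
- n=12, a=5: 2×792/42,504 = .037
- n=17, a=4: 2×2,380/46,376 = .103
- n=17, a=5: 2×6,188/278,256 = .044

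The threshold against zero is 5 events at either size. Against one event it is 7. No assumed AE rate enters this step.

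**Step 2: power.** Sum the product of the two binomial probabilities over all tables with Fisher P<.05. When the reference rate is 0%, this reduces to P(X≥5). For example, n=12 and 50% gives 1 − (1+12+66+220+495)/4,096 = 1 − 794/4,096 = .806.

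| Assumed true AE rates | 12 per arm | 17 per arm | 24 eyes per arm, taken as independent |
|---|---|---|---|
| 0% v 20% | 7.3% | 24.2% | 54.0% |
| 0% v 30% | 27.6% | 61.1% | 88.9% |
| 0% v 50% | 80.6% | 97.5% | 99.9% |
| 5% v 20% | 4.1% | 11.6% | 23.7% |
| 5% v 30% | 16.3% | 34.7% | 56.0% |
| 10% v 30% | 9.5% | 18.6% | 31.4% |

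At 12 per arm, 80% power needs a true rate of about 50% against 0%, 61% against 5%, or 69% against 10%. Conversely, 80% power for 5% v 20% needs 76 per arm (88 with continuity correction).

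**Step 3: other readings of the planned test.** The uncorrected chi-square at 12 per arm is more permissive: significant from 4 v 0, with power 12% for 5% v 20% and 51% for 0% v 30%. With so few events the expected counts are small (4 events in 24 participants is 2 expected per arm), which is where Fisher is normally chosen. An exact three-arm test gives P=.025 for 0, 0, 4 events, P=.086 for 0, 4, 4 and P=.039 for 0, 5, 5.

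**Step 4: what intervals would show.** After zero events, the exact upper limit is 1 − .05^(1/n) one-sided or 1 − .025^(1/n) for a two-sided 95% interval.
- 0/12: 22.1% and 26.5%
- 0/17: 16.2% and 19.5%

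Risk differences at 12 per arm (Newcombe 95% interval, percentage points):
- 0/12 v 0/12: 0 (−24 to +24)
- 1/12 v 1/12: 0 (−28 to +28)
- 0/12 v 3/12: +25 (−4 to +53), Fisher P=.22
- 0/12 v 4/12: +33 (+2 to +61), Fisher P=.093

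**The case against.** Four stronger readings are tempting, and the document supports none of them.

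- *The AE test is the trial's only safety inference.* It is not. Visual acuity and the Quality of Vision Questionnaire, with its pain and discomfort scores, are also compared before and after massage. The Fisher power figures do not apply to those scores. They do not bound the rate of keratitis, conjunctivitis or the other events listed under Classification of AEs, so the point holds for AE incidence.
- *The test is there to ensure safety.* That clause opens the descriptive sentence, not the testing one. The stated objectives are IOP and Schlemm canal morphology. Participant protection rests on examination, suspension, withdrawal and follow-up of events.
- *P>.05 will be read as equally safe.* A reader might infer this from the Background, but no such rule is written. The Discussion and the Future Directions section both leave safety to later work.
- *The test misses harm of any size.* It does not: 0% v 50% has 81% power at 12 per arm.

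It can also fairly be said that low AE power is usual in a small trial sized on another outcome, that chi-square and Fisher tests are conventional and valid, and that interval methods often sit in a statistical analysis plan. This keeps the point minor. It does not remove it: the article does fix a method for AE incidence, that method is the less informative one, and the general mention of a 95% CI does not supply the missing interval.

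**Conclusion.** The concern holds in a narrow form. A chi-square or Fisher test is the only stated inference on AE incidence. At the planned arm size it needs at least 5/12 against 0/12, and it has about 4% power for 5% v 20% and 28% for 0% v 30%. At about 17 per arm these rise to 12% and 61%. Even counting 24 eyes as independent leaves 24% for 5% v 20%. A nonsignificant result is the likely outcome if AEs are as rare as the authors expect, and it would carry little information about comparative safety.

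The power figures rest on assumed AE rates, a two-arm contrast and participants as the unit. The 5 v 0 threshold and the zero-event limits need no assumed rate. This is an inexpensive improvement in reporting. It is not an error in the test, and the primary IOP result is unaffected.

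**What to change.** In Statistical Methods, make estimation the basis of AE reporting:

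1. For each arm, including no massage, give the number and percentage of participants with at least one AE, with an exact (Clopper-Pearson) 95% CI.
2. Give between-arm risk differences with 95% CIs. Name the contrasts and the interval method in advance: the 0/12 v 4/12 example shows that a Newcombe interval can exclude zero while Fisher's P exceeds .05.
3. Keep any chi-square or Fisher P value as secondary, and state that P>.05 will not be interpreted as similar safety.

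The cost is two or three sentences and a few intervals from data already collected. The drawback is a less reassuring safety statement: an arm with no events in 12 participants would be reported as compatible with AE rates up to about 22% (one-sided) or 26.5% (two-sided).

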### Ethical Considerations

This study will adhere to the ethical principles outlined in the Declaration of Helsinki and has been approved by the TMUEH Institutional Review Board (2024KY-56). Informed consent will be obtained by clinical physicians who have received specialized training. Written informed consent will be obtained from all participants before their participation. All information and clinical data, including participants’ personal medical histories, will remain confidential.

### Monitoring

The trial steering committee, comprising project leaders and key decision-makers, is responsible for overseeing and supporting the study. This committee will provide strategic guidance throughout all phases of the research and will be responsible for preparing and submitting the final study report.

Given the low likelihood of AEs in healthy participants, a data monitoring committee will not be established. Data collection and management will be conducted using a Microsoft Excel (version 16) database, which will be regularly updated in accordance with the study protocol.

Any modifications to the inclusion criteria or test procedures will be submitted to the TMUEH Medical Ethics Review Committee for review and approval before implementation.

### Classification of AEs

Any unexpected symptoms or signs that may pose a risk to the physical or mental well-being of participants will be classified as AEs. Localized AEs may include intolerable dry eye symptoms, keratitis, severe corneal ulcers, conjunctivitis, eye irritation, and blurred vision. Mild AEs, such as temporary dry eyes or foreign body sensation, which do not affect daily activities, will be managed by suspending the intervention, administering artificial tears, and re-examining participants after 30 minutes. Moderate AEs, such as conjunctivitis or slightly elevated IOP, will be managed by suspending the treatment, referring to the PI, providing targeted treatment, and following up until the symptoms resolve. In the event of a serious AE, the PI and the TMUEH Medical Ethics Review Committee will be promptly notified, the trial will be immediately suspended, and appropriate medical intervention will be provided to ensure participant safety and minimize further risk.

### Auditing Trial Conduct

This study will be subject to weekly evaluations and assessments conducted by independent supervisors to ensure compliance with the research protocol and ethical standards.

### Dissemination Plans

The research findings will be disseminated to relevant stakeholders, including participants, their families, physicians, advisory committees, and medical boards. In addition, the results will be shared through high-impact medical journals and presentations at international medical conferences to ensure broad academic and clinical engagement.

## Results

As of July 15, 2025, the study recruited 50 participants, and all provided written informed consent. The initial results are anticipated to be reported and published after the completion of data collection and analysis, with publication expected in 2025-2026.

## Discussion

### Summary

Eye massage is commonly used for relaxation, relief of eye strain, and the management of dry eye syndrome [19,30]. However, improper technique or excessive pressure can lead to ocular complications [20,31]. A case study by Yadgari et al [32] reported the formation of an intracorneal cleft after ocular massage in a patient who had undergone Ahmed valve implantation for glaucoma, highlighting the risk of corneal structural damage when excessive external pressure is applied to the eye. Riede-Pult et al [33] investigated the short-term effects of eyelid massage on corneal shape using topographic analysis. Although the study found no significant short-term changes in corneal curvature or visual acuity, it did not assess potential long-term consequences, suggesting that while brief eyelid massage may be safe, repeated or forceful manipulation could carry risks. A systematic review by Yin et al [34] explored the adverse effects of massage therapy in pain-related conditions. Reported complications included soft tissue trauma, nerve injury, and vascular complications, which could theoretically apply to forceful eye massage as well. The possibility of pressure-induced damage to the delicate ocular and periocular structures warrants caution. Lee et al [30] conducted a randomized controlled trial comparing a thermal eye massager with artificial tears to treat dry eye syndrome. While the thermal massage was found to be effective and generally safe, some patients experienced mild and transient adverse effects such as irritation or temporary discomfort. A broader review assessed the safety of massage therapy and highlighted rare but serious adverse effects such as vascular damage, nerve compression, and eye trauma [24,35]. While these events are uncommon, they emphasize the importance of appropriate technique and caution when applying pressure around the eyes [25,26,36,37]. This study will enroll only healthy adult participants with IOP within the target range of 10 to 21 mm Hg and no ocular comorbidities to minimize confounding factors and ensure a controlled baseline for evaluating the isolated effects of ocular massage on the SC and IOP. However, we acknowledge that this limits the generalizability of the findings, particularly to populations with glaucoma or postsurgical eyes, where ocular massage may be used therapeutically. Future studies in these clinical populations are warranted to validate the safety and efficacy of these interventions under real-world conditions. In this randomized controlled trial, participants were randomly assigned to 1 of 3 groups (digital ocular massage, EyePeace ocular massage, or no ocular massage) and underwent baseline and 10-minute postintervention assessments using AS-OCT and IOP measurements. These short-term findings could inform novel, nonpharmacological approaches for glaucoma risk mitigation. However, the short follow-up window limits conclusions regarding durability. Future work should incorporate longer follow-up periods, include patient populations with glaucoma or ocular hypertension, and explore the correlation between morphological changes and sustained IOP regulation. Safety assessments and comparative efficacy in real-world clinical settings remain crucial.

A more extended follow-up period is needed to determine the long-term effects of digital ocular massage and EyePeace ocular massage on IOP and anterior segment anatomical changes. It is also unclear whether the changes in IOP, anterior segment anatomy, and vision are sustained for long periods and can be considered long-term therapy. This study is a single-masked clinical trial; therefore, potential bias may still be present, despite the researcher’s objective evaluation of data. In addition, as this study measures outcomes only 10 minutes after the intervention, it may not capture the longer-term persistence or fluctuation of the IOP-lowering effect. Future studies with extended follow-up periods (eg, 30 minutes, 1 hour, or longer) are warranted to assess the duration and stability of the responses.

### Future Directions and Conclusions

Although gentle eye massage can offer therapeutic benefits, excessive or improper pressure may lead to corneal damage, intraocular structural issues, soft tissue trauma, and vascular complications. Patients with preexisting ocular conditions (eg, glaucoma, keratoconus, or recent eye surgery) should exercise caution and seek medical advice before eye massage. More research is needed to fully understand the long-term implications of repeated ocular massage on eye health, including the durability of IOP reduction, cumulative tissue effects, and optimal massage parameters. Future clinical trials involving diverse patient populations and extended follow-up periods will be essential to determine the safety and efficacy of ocular massage as a nonpharmacological therapeutic strategy.

## Data Availability

The datasets generated and analyzed during this study will be available from the corresponding author on reasonable request.

## Appendix

Multimedia Appendix 1 Modified Quality of Vision Questionnaire.

## Abbreviations

AE: adverse event
AS-OCT: anterior segment optical coherence tomography
IOP: intraocular pressure
PI: principal investigator
SC: Schlemm canal
SPIRIT: Standard Protocol Items: Recommendations for Interventional Trials
TM: trabecular meshwork
TMUEH: Tianjin Medical University Eye Hospital
